**Primary outcomes**								
	Medication adherence	Vaica (time-stamped)	✓	✓	✓	✓	✓	
	BP^a^	Clinic resting SBP^b^	✓	✓	✓	✓	✓	✓
**Secondary outcomes**								
	Therapeutic Inertia	Provider adherence to KDIGO^c^ goals: Timely medication changes (date of medication change following medication adherence) and BP feedback (biweekly SMASK^d^ reports for SMASK participants) and from clinic visits for all subjects (Figure 2)	Weekly^e^	Weekly^e^	Weekly^e^	Weekly^e^	Weekly^e^	Weekly^e^
	Self Determination Theory Constructs	TSRQ^f^ autonomous self-regulation [51,52] (α=0.81-0.84; correlation with GCOS^g^: *r*=0.38, *P*<.001; correlation with HCCQ^h^: *r*=0.38, *P*<.001), weight loss attendance (*r*=0.34, *P*<.001), body mass index (*r*=-0.11, *P*<.05), 18-month test-retest autonomous (*r*=0.47), controlled items (*r*_s_=0.34]) [53], correlation with medication adherence (*r*=0.58, *P*<.001)] [54]	✓			✓	✓	✓
**Exploratory outcomes**								
	eGFR^i^	GFR^j^ estimation equations [55,56]	✓	✓	✓	✓	✓	✓
	Ambulatory BP	24-h ambulatory BP with SpaceLabs 90207		✓			✓	✓
	**Methodological parameters**							
		Recruitment and retention rates: patient/provider satisfaction and usefulness scale (TSUQ^k^) [57] (satisfaction: α=0.96; usefulness: α=0.92; 1-week test-retest *r*=0.98 [58])					✓	
		Fidelity checklists: patient level (eg, connection/reloads of Vaica, BP uploads via phone, and opening of messages/education information) and provider level (eg, opening of patient summary reports and phone alerts)						
	Ancillary medication adherence measures	Medication possession rate	✓	✓	✓	✓	✓	✓
**Potential moderators/mediators**								
	Demographics	Age, education level, income, type of health care insurance	✓		✓	✓	✓	✓
	Anthropometrics	Height, weight, girth	✓	✓	✓	✓	✓	✓
	Health literacy	Health Literacy Scale [59-62], correlated with short test of functional health literacy in adults. Three questions compared to those in the Short Test of Functional Health Literacy in Adults to detect inadequate health literacy: areas under the receiver operating characteristic curve were 0.76, 0.80, and 0.87. When correlated with Short Form-36 (*r*=0.86-0.87), it differentiates between healthy status and various types of illnesses (eg, migraine vs healthy using components: physical and mental quality of life; all *P*<.001)	✓					
**Adverse events**							
	Medication Side Effects Scale [63,64]	✓	✓	✓	✓	✓	✓
	Hypertension/immunosuppression knowledge [59,65] (α=0.70, high-low correlation: *P*<.01)	✓					
	Short Form-8 (α=0.87)	✓	✓	✓	✓	✓	✓
	Perceived Stress Scale (α=0.84-0.86; 2-day test-retest *r*=0.85) [64]	✓	✓	✓	✓	✓	✓

^a^BP: blood pressure.

^b^SBP: systolic blood pressure.

^c^KDIGO: Kidney Disease Improving Global Outcomes.

^d^SMASK: Smartphone Medication Adherence Saves Kidneys.

^e^Weekly SMASK reports and from clinic visits for all subjects.

^f^TSRQ: Treatment Self-Regulation Questionnaire.

^g^GCOS: General Causality Orientations Scale.

^h^HCCQ: Health Care Communication Questionnaire.

^i^eGFR: estimated glomerular filtration rate.

^j^GFR: glomerular filtration rate.

^k^TSUQ: Telemedicine Satisfaction and Usefulness Questionnaire.

### Clinic Resting Blood Pressure

BP evaluations will be conducted at enrollment; randomization; and 1, 3, 6, and 12 months. Patients will be seated upright with right arm resting on a table at heart level and a proper cuff size will be fitted. A Dinamap Pro-Care 200 BP device (GE Healthcare, Buckinghamshire, United Kingdom) will be used to take the clinic BP measurements. The Dinamap has been validated following standard auscultatory methods from the British Hypertension Society and the Association for Advancement of Medical Instrumentation [66]. The Dinamap, as well as all other BP devices used in the trial, are calibrated according to the manufacturers’ specifications. A reading will be taken immediately, after 5 minutes of rest, and following a 2-minute interval. The average of the last two readings will be used in the analyses. Subjects in the SMASK group will use the same protocol (ie, a series of 3 BP readings with 5 and 2 minutes in between the first and second readings and between the second and third readings, respectively) at home for BP self-monitoring. This functionality will be embedded within the SMASK app and automatically guide the participants through the protocol with audio guides, timer count downs, and chimes when each waiting period is complete.

### Outcome Measures

#### Primary Outcome Measures

These include proportion of participants achieving success in meeting and sustaining adherence to the KDIGO guidelines for SBP control (resting SBP <130 mm Hg) and proportion of participants meeting and sustaining monthly medication adherence scores >0.90.

#### Secondary Outcome Measures

These include provider adherence to KDIGO guidelines, as measured by the appropriateness and timeliness of BP medication changes, and subjects’ self-report of changes in self-determination theory tenants (ie, self-efficacy and autonomous motivation).

#### Exploratory Outcome Measures

These will include changes in estimated glomerular filtration rate (eGFR) and variability of CNI trough levels (%cv). CNIs have a well-described high inter- and intrapatient variability as well as a narrow therapeutic index. For these reasons, among others, therapeutic drug monitoring of CNI is the standard of care in solid organ transplantation and guides all CNI titrations [67,68]. Changes in the 24-hour ambulatory BP will also be examined.

### Participant Timeline

A timeline for participant recruitment, intervention, and follow-up assessments is shown in Figure 1.

### Proposed Sample Size

To evaluate SMASK treatment efficacy, 80 patients will be recruited and randomly assigned to either SMASK or SC. The primary outcomes of aim 1 include the proportion of patients with >0.90 medication adherence scores (based on the date/time stamped scores from the electronic trays) and proportion of patients meeting and sustaining adherence the KDIGO guidelines for clinic-based SBP control (<130 mm Hg). In intent-to-treat (ITT) analysis, with 40 patients per group, a two-sided Chi-square test (α=0.05) will have >90% power to detect a difference of 35% in proportions of those who are medication adherent (or meeting and sustaining adherence to the KDIGO BP guidelines) in the SMASK group compared to those in the SC group at the 3-month time point. A difference of 35% in medication adherence between the groups would be considered clinically relevant and warrant changes in clinical practice. Conservative estimates for medication adherence and expected BP control proportions will be used for power calculations. This approach was taken with a small pilot study, and CIs on effect sizes were quite large. Medication adherence observed in the SMASK 3-month feasibility study was 89% (versus 0% in control group; N=19). For the clinic resting BP control, we observed that 90% versus 10% of the participants controlled BP in the SMASK and control groups, respectively. Overall attrition was 10% in the intervention group [69].

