**Methods:**

This two-arm, 6-month, phase II single-site efficacy RCT will involve 80 kidney transplantation recipients. Participants will be randomly assigned to the SMASK intervention arm or control arm. SMASK includes multilevel components: automated reminders from an electronic medication tray; tailored text messages and motivational feedback, guided by the self-determination theory; and automated summary reports for providers. Evaluations will be conducted preintervention, at 3 and 6 months, and posttrial at 12 months. Specific aims are to test the hypotheses that compared to standard care, the SMASK cohort will demonstrate significantly improved changes at 3, 6, and 12 months in the primary outcome variables medication adherence (proportion with electronic monitor-derived score >0.90) and blood pressure control (proportion meeting and sustaining adherence to the Kidney Disease Improving Global Outcomes [KDIGO] guidelines for blood pressure control); the secondary outcome variables provider adherence to KDIGO guidelines, measured by timing of medication changes and changes in self-determination theory constructs; and the exploratory outcome variables estimated glomerular filtration rate, variability in calcineurin inhibitor trough levels, and proportion of patients meeting and sustaining the 24-hour ambulatory blood pressure below 130/80 mm Hg. After the 6-month evaluation, interviews with a random sample of SMASK subjects (n=20) and health care providers (n=3-5) will assess user reactions including acceptability, usability, and aids/barriers to sustainability. Data from the RCT and interviews will be triangulated to further refine and optimize SMASK and prepare for a multisite effectiveness RCT.

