The authors concluded that research on medication adherence programs in the transplant population is misguided in that it often does not include patients verified as having poor medication adherence, lacks the use of programs that are engaging and foster sustained regimen adherence, and does not evaluate clinically relevant transplant-specific outcomes. Our work has addressed several of these issues including identification and recruitment of kidney transplant recipients with verified poor medication adherence using multiple indices. We chose to employ a two-part screening process including BP measurement and one-time medication adherence via medication possession ratio screening followed by a 1-month screening to determine medication nonadherence via a Bluetooth-enabled electronic pill box with audio and visual alerts disabled. In a pilot study, we found that 70% of otherwise eligible kidney transplant recipients were medication nonadherent [25], and thus far, we have identified a higher (~82%) proportion of such recipients in this RCT. Although medication nonadherence is on a continuum, it has been well demonstrated that even small degrees of medication nonadherence have negative effects on kidney transplant recipient outcomes [16-18]. We have employed a patient-centered, theory-guided, iterative design process to develop a medical regimen self-management program aimed at fostering self-efficacy and autonomous motivation to help ensure regimen adherence is sustained. In light of the expense and length of follow-up necessary to demonstrate significant clinical outcome improvements (eg, reduced acute rejection, graft loss, and death), we have adopted a strategy to investigate surrogate markers that are shown to be strongly predictive of worsened long-term outcomes (ie, BP and percent coefficient of variation [%cv]) [36-44]. A recent review of the literature on hypertension management in kidney transplant recipients concluded that posttransplant hypertension is prevalent (70%-90%), multifactorial, and rarely controlled (~33%) [8]. Specifically, among kidney transplant recipients at our transplant center, we found the prevalence of hypertension to be 95%, with only 34% having met the Kidney Disease Improving Global Outcomes (KDIGO) guidelines for hypertension control at a mean follow-up of 7.3 (SD 4.5) years after transplant [45]. Uncontrolled hypertension remains a significant problem in kidney transplant recipients; thus, efficacious intervention programs are warranted.

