### Statistical Analyses

#### Primary Outcome Measures

The ITT analysis set will be determined in accordance with the International Conference on Harmonization E9 Guideline “Statistical Principles for Clinical Trials” [70] and will include all randomized subjects. For all subjects included in the ITT analysis set, all available data points will be included in the model. We chose a mixed-effects model approach because this method is a standard method in RCTs and can handle missing data and account for correlated data such as repeated measurements within patients or patients clustered within providers [71-73].

We propose a two-level analysis strategy: Our primary analysis will include the simple mixed-effects model containing the fixed time and intervention group, time, and time-by-intervention as primary independent variables (fixed effects) and MD as a random effect to account for clustering. The main analysis will compare the two intervention groups (SMASK vs SC) at the primary time point outcome at 3 months. We will estimate medication adherence score changes and changes in resting and 24-hour BP for each subject over the trial (preintervention and 1, 3, 6, and 12 months) and the within-subject longitudinal trajectories (eg, slopes) and summarize the mean longitudinal trajectory within each group. Intraclass correlations and variance estimates will be obtained for the efficacy outcomes and covariance structure of the longitudinal scores to determine the sample size (and hence adequate power) for a future effectiveness RCT.

In secondary/exploratory analysis for aim 1 outcomes, the potential influence of *a priori* specified covariates on these models will be explored, including self-determination theory tenants, demographic and clinical characteristics, and comorbidities. In an additional exploratory analysis, effect modifications of covariates will be examined through inclusion of covariate-by-group interaction terms in the multivariable models.

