## Results

The SMASK project received funding from NIDDK in June 2016, obtained institutional review board approval in April 2016, and began data collection in July 2016. As of July 2018, we have completed enrollment with a total sample size of 80 participants. Currently, we are analyzing baseline data and upon completion of analysis of the final participant in the 6-month active trial, we will begin analyzing preliminary data to be submitted for peer-review publication.

Approval for important protocol modifications will be sought from the institutional review board. Written informed consent was obtained from all patients before enrollment by a trained research coordinator. There are no anticipated risks associated with participation in the study. Patients are free to withdraw at any time. Data will be kept confidential and anonymized for analyses.

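### Each of two primary outcomes is given the full two-sided 0.05 with no multiplicity rule, the primary time point is stated inconsistently, and the >90% power makes no allowance for attrition

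*Protocol article*

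**What the plan says.** The protocol article names two primary outcomes (Outcome Measures, and again in Proposed Sample Size): the proportion with adherence scores above 0.90, and the proportion meeting and sustaining resting SBP below 130 mm Hg.

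- **Power.** Proposed Sample Size gives one statement for both outcomes at month 3. "with 40 patients per group", it says, "a two-sided Chi-square test (α=0.05) will have >90% power to detect a difference of 35% in proportions" of adherent patients, with blood pressure control added in parentheses as the alternative.
- **Numbers.** "80 patients will be recruited and randomly assigned to either SMASK or SC", so 40 per group is everyone randomised. The Results section confirms that "we have completed enrollment with a total sample size of 80 participants".
- **Attrition.** The same sample-size paragraph reports from the pilot that "Overall attrition was 10% in the intervention group". The figure is not applied to the sample size or to the power.
- **Planning rates.** They are called conservative but not given. The pilot rates are: adherence 89% vs 0%, blood pressure control 90% vs 10%.
- **Time point.** The abstract says the SMASK cohort "will demonstrate significantly improved changes at 3, 6, and 12 months in the primary outcome variables". Statistical Analyses compares the groups "at the primary time point outcome at 3 months".

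**The concern.** Three gaps bear on what a positive result would mean.

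1. With two primary outcomes each tested at 0.05 and no rule joining them, the trial has two chances at a primary claim. The 5% level then holds for each outcome separately but not for the trial's conclusion.
2. The abstract's three time points add further chances unless the body's choice of month 3 governs.
3. The power figure equates patients randomised with patients evaluable. Statistical Analyses uses all available data points, and the only imputation described is for exploratory outcomes, so a patient without month-3 data adds less than the calculation assumes.

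At stake are the false-positive rate of a trial meant to justify a multicentre successor, and whether a reader can rely on the stated power when the control rate behind it is not given.

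**Working it through.** **Inputs.** From Proposed Sample Size: 40 per arm, two-sided alpha 0.05, chi-square test, 35-point difference, pilot attrition 10% in one arm, pilot control rates 0% and 10%. Assumed here: the planning control rate p0 (not stated, so varied), and 10% attrition in both arms, giving 40 × 0.90 = 36 per arm.

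**1. Familywise error, two outcomes at month 3, each at 0.05.**
- Independent tests: 1 − 0.95² = 0.0975.
- Correlated tests: 1 − P(|Z1| < 1.96 and |Z2| < 1.96) with bivariate-normal statistics gives 0.091 at correlation 0.5 and 0.070 at 0.9.

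**2. The plan's own power figure.** Exact power of the uncorrected Pearson chi-square is the sum, over all pairs of responder counts that reject, of Bin(x; n, p0 + 0.35) × Bin(y; n, p0). With 40 per arm at 0.05 the minimum is 90.4%, at 32.5% vs 67.5%. The >90% claim therefore reproduces at every control rate. The pooled normal approximation gives a minimum of 89.4%. With a continuity correction or Fisher's exact test the minimum is 85.8%.

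**3. Power after attrition (exact).**

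| Control rate | 40/arm, 0.05 | 36/arm, 0.05 | 36/arm, 0.025 |
|---|---|---|---|
| 0% | >99% | >99% | >99% |
| 10% | 96.0% | 93.9% | 89.9% |
| 20% | 91.5% | 88.8% | 81.2% |
| 32.5% | 90.4% | 85.0% | 78.4% |
| 45% | 91.5% | 88.8% | 81.2% |
| 55% | 96.0% | 93.9% | 89.9% |

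With 36 per arm at 0.05, power is below 90% for control rates of about 18% to 47%.

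**4. What Holm would cost.** The 0.025 column is the power of the first Holm step, so it is a lower bound. Once one outcome passes, the other is tested at 0.05. For independent outcomes that both have the 35-point effect, per-outcome Holm power is b1 + (a1 − b1) × b2. Here a1 and b1 are this outcome's power at 0.05 and 0.025, and b2 is the other outcome's power at 0.025. With 36 per arm:
- Control rate 10%, other outcome also 10%: 0.899 + (0.939 − 0.899) × 0.899 = 0.935. With the other outcome at 0%: 0.899 + 0.040 × 0.999 = 0.939.
- Control rate 34% (mid-range), other outcome 10%: 0.784 + (0.851 − 0.784) × 0.899 = 0.844. With the other outcome at 0%: 0.784 + 0.067 × 0.999 = 0.851.

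**5. If both outcomes had to succeed.** Each may be tested at 0.05 and the joint error stays within 5%. Joint power with independent outcomes and 36 per arm is 0.939² = 0.88 with both control rates at 10%, and 0.850² = 0.72 with both at 32.5%. With control rates of 0% and 10% it is about 0.94.

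**The case against.** The strongest reply has three parts.

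**The decision rule.** The parenthetical in the power statement may show only that one calculation serves both outcomes. The Objective and the Conclusions join adherence and blood pressure control with an and. If both must succeed, no adjustment is needed. A multiplicity rule is also commonly left to an analysis plan, and this is a phase II trial. Part of this stands: the article does not say that either outcome suffices, so the 9% to 9.75% is conditional on that reading. But it does not say that both are required either. Because 0.05 is written into the power statement, a later Holm step or a both-must-succeed rule would change the published power. That goes beyond detail left to another document.

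**The power.** A reader might infer that the >90% figure is wrong. It is not: it reproduces, and after 10% attrition in both arms it still exceeds 90% at both pilot control rates. If only the intervention arm loses 10% (36 vs 40), exact power is 95.1% at a 10% control rate and 91.1% at 20%. A reader might also take the centre's figure, "only 34% having met the Kidney Disease Improving Global Outcomes (KDIGO) guidelines for hypertension control", as the expected control-arm rate. It describes the centre's recipients in general, at a mean of 7.3 years after transplant. This trial enrols only patients with SBP of at least 130 mm Hg at both screening and baseline and adherence below 0.85. In the Holm arithmetic 34% serves only as a mid-range value.

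**The time points.** A reader might count two outcomes at three visits as six tests, with 1 − 0.95⁶ = 0.265. The documents do not support this. Table 1 schedules no electronic-tray adherence at 12 months, and both Proposed Sample Size and Statistical Analyses fix month 3. What stands is the inconsistency in the abstract.

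**Conclusion.** The concern holds in limited form.

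- **Error rate.** As written, the familywise 5% level is not protected. If either outcome can support efficacy, the month-3 error is about 9% to 9.75% for correlations from 0.5 down to 0, and 7% at correlation 0.9.
- **Time points.** The abstract's 3, 6 and 12 months conflict with month 3 as primary in the body and should be reconciled.
- **Power.** The >90% figure is correct for 40 evaluable per arm but carries no allowance for attrition and rests on an unstated control rate. With 36 per arm at 0.05 it drops below 90% only for control rates of about 18% to 47%, with a minimum of 85%. The loss in both arms is an assumption, since the 10% is a pilot figure for the intervention arm.

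This should be corrected, but it does not invalidate the design. The Results section describes analysis of baseline data only, so the rule can still be fixed before outcomes are analysed.

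**What to change.** 1. Name month 3 as the only confirmatory time point in the abstract, aims and analysis, and label months 6 and 12 secondary. Note that tray adherence is not scheduled at month 12.
2. Test the two primary outcomes by Holm at an overall two-sided 0.05. Alternatively, state that both must succeed, and give joint power.
3. State the assumed control rate for each outcome and restate power with 36 evaluable per arm: about 85% to 94% at alpha 0.05 for control rates of 10% to 55%, and above 99% at 0%.
4. If Holm is adopted, give 78% to 90% (alpha 0.025, same range of control rates) only as the first-step lower bound. Report per-outcome Holm power beside it: about 93% to 94% at a 10% control rate and 84% to 85% at mid-range rates, with both effects present and independent outcomes.

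The cost is wording, a less favourable stated power and a stricter first test. No more patients are needed.

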### Recruitment

Eligible patients were identified from hospital medical records by a research assistant. A research coordinator approached potential subjects in the kidney transplant clinic and obtained voluntary informed consent from patients who were interested in participating. After obtaining informed consent, the clinic resting BP protocol was conducted (see Clinic Resting Blood Pressure) and if SBP ≥130 mm Hg, the subject completed a set of questionnaires (Table 1) and was instructed to wear a SpaceLabs 90207 ambulatory BP monitor (SpaceLabs, Inc, Issaquah, WA) for 24 hours. The subject then began the 1-month screening period, as described above. The study site performs approximately 20 kidney transplants per month. We provide a smartphone and an internet data plan for the SMASK subjects who do not own a smartphone compatible with the SMASK app.

### Allocation and Concealment

Subject randomization will be stratified by race and gender and will be conducted by a statistician using a computer-generated random sequence of numbers. Participants who consent to the study and are eligible for randomization at the conclusion of the 1-month medication intake screening period are allocated to either the intervention (SMASK) or SC arm using the computer-generated randomization sequence. Each random sequence is kept concealed in an envelope that is opened by the research coordinator at the time of randomization.

